# FUNDER DETAILS

| **FUNDER(S)** | **FINANCIAL AND NON-FINANCIAL SUPPORT GIVEN** |
| --- | --- |
| NIHR Applied Research Collaboration (ARC) East Midlands | £ 65,618.17 |
| University of Lincoln | In-kind contributions from Professors [name] (5% FTE), and [name] (5% FTE). |
| University of Leicester | In-kind contributions from [name] (5% FTE). |
|  | There is an additional contribution of £1000 from [name] via his NIHR Senior Investigator Award. |

# STUDY SUMMARY

| Study Title | Effect of implementing an ambulance clinician delivered hypoglycaemia intervention (‘Hypos can strike twice’) on repeat ambulance calls, attendances and transportation to hospital: non-randomised stepped wedge and process evaluation |
| --- | --- |
| Study Design | Non-randomised stepped wedge design with mixed-methods process evaluation. |
| Study Participants | **Patients**  Young adults aged 16-17 years and adults aged 18 years+ with diabetes experiencing hypoglycaemia needing an ambulance service response.  **Clinicians**  Ambulance staff providing treatment and advice to people who have had a hypoglycaemic attack. |
| Eligibility Criteria | **Patients**  Young adults aged 16-17 years and adults aged 18 years+ with diabetes experiencing hypoglycaemia needing an ambulance service response. Hypoglycaemia for this study was identified as a ‘clinical impression’ of ‘hypoglycaemia’ or ‘diabetic problem’. Hypoglycaemia may also be identified according to ambulance guidelines^1^ as any blood glucose less than 4mmol/L.  **Clinicians**  Ambulance staff providing treatment and advice to people who have had a hypoglycaemic attack. |
| Planned Sample Size | Interviews: 10-15 staff and 10-15 patients, based on previous experience of the sample required to achieve theoretical saturation.  Survey: We will survey all front-line staff. The estimated sample size for patients is 447. |
| Study Duration | 12 months |
| Objectives | Aim: To evaluate the effect of implementing the ‘Hypo’s can strike twice’ intervention to patients with diabetes and hypoglycaemia attended by East Midlands Ambulance Service NHS Trust in the East Midlands region.  Objectives: To investigate the effect of implementing the ‘Hypo’s can strike twice’ on:   1. Repeat ambulance calls and attendances for hypoglycaemia; 2. Recorded referrals to an appropriate healthcare professional (e.g. GP, nurse); 3. Completed care bundle for hypoglycaemia (proportion of patients with all of blood glucose recorded before treatment, blood glucose recorded after treatment and treatment given for hypoglycaemia; 4. Costs of implementation ‘Hypo’s can strike twice’ intervention vs costs of health service resource use; 5. To conduct a process evaluation to explore how ‘Hypo’s can strike twice’ exerts its effects and can be scaled up if effective by understanding implementation, mechanisms of impact, and contextual factors using interviews and surveys. |
| Outcomes | Primary outcome   1. Repeat ambulance calls and attendances for hypoglycaemia within 14 days.   Secondary outcomes   1. Repeat ambulance calls and attendance for hypoglycaemia within 30 and 90 days. 2. Recorded referral to an appropriate healthcare professional (e.g. GP, nurse). 3. Completed care bundle for hypoglycaemia (proportion of patients with all of blood glucose recorded before treatment, blood glucose recorded after treatment and treatment given for hypoglycaemia. 4. Costs of implementation of ‘Hypo’s can strike twice’. 5. Process evaluation to explore how ‘Hypo’s can strike twice’ exerts its effects and can be scaled up if effective by understanding implementation, mechanisms of impact, and contextual factors using interviews and surveys |
| Data Analysis | Work package (WP) 1 Stepped wedge: Dispatch data will be linked with clinical data using a unique job number. People included will be identified and tracked for repeat attendances. In the stepped wedge design, the intervention and control observation periods take the place of the treatment and control groups in a parallel trial and the distribution of results across unexposed observation periods is compared with that across the exposed observation periods. There are a small number of steps and so characteristics of the groups in the wedge can be compared by group, including number, the average cluster size, cluster characteristics, and important patient characteristics.  Following an intention-to-treat principle, clusters will be analysed according to their crossover time irrespective of whether crossover was achieved at the desired time. Under the stepped wedge design the evaluation happens over a period of time, during which the number of clusters exposed to the intervention gradually increases. This means that unexposed observations will, on average, be from an earlier calendar time than exposed observations. Additionally, policy and service delivery changes may occur. Calendar time is associated with both the exposure to the intervention and also possibly the outcome, and so is a potential confounder and will be adjusted for in the analysis.  A linear mixed model will be fitted adjusting for the systematically different observation periods and for clustering in the data. Time is included as a fixed effect and a random effect for cluster. The design also allows examination of the impact of the intervention changing over time once it is introduced into a cluster.  WP2 Health economics: We will use a cost consequences model, estimating costs from NHS Reference Costs to evaluate the costs of the intervention in relation to its effects. Key cost drivers associated with repeat hypoglycaemic episodes will be modelled.  WP3 Survey: We will analyse the overall experience of both patients and ambulance staff, as well as use descriptive statistics and comparisons between responder groups (e.g. ambulance staff vs patients; paramedics vs emergency medical technicians), where appropriate.  WP4 Qualitative: Qualitative data analysis will involve thematic coding of collected data (i.e. framework analysis) and the audio recorded data (transcribed verbatim) will be entered into NVivo 11 qualitative data analysis software to facilitate analysis. We will use the Medical Research Council guidance^2^ on process evaluations of complex interventions as a framework to guide the analysis and synthesis of our data, complemented by inductive codes to ensure all aspects of the participants’ experience are fully captured. Accordingly, our framework will be developed based on the following key components and functions of a process evaluation: description of the intervention and its causal assumptions; the implementation process (how delivery was achieved, training, resources, etc.) and what was delivered (fidelity, adaptations, etc.); the mechanisms of impact (participant responses to and interactions with the intervention, mediators, unexpected pathways and consequences), context (contextual factors that shape theories of how the intervention works and that affect the implementation, intervention mechanisms, etc.); and outcomes.  WP5 Integration: We will integrate qualitative and quantitative data to explain the findings from the stepped wedge and economic evaluation using the interview and survey findings. |

# KEY WORDS

Ambulance calls; diabetes; hypoglycaemia; intervention; leaflet; process evaluation.

# LIST OF ABBREVIATIONS

AE Adverse Event

CF Consent Form

CI Chief Investigator

CRF Case Report Form

EMAS East Midlands Ambulance Service NHS Trust

GCP Good Clinical Practice

HRA Health Research Authority

ICF Informed Consent Form

ISF Investigator Site File (This forms part of the TMF)

ISRCTN International Standard Randomised Controlled Trials Number

LIH Lincoln Institute for Health

NHS R&D National Health Service Research & Development

PI Principal Investigator

PIS Participant Information Sheet

PPI Public and Patient Involvement

REC Research Ethics Committee

SAE Serious Adverse Event

SOP Standard Operating Procedure

TMF Trial Master File

UoL University of Lincoln

# STUDY MANAGEMENT

### ROLE OF STUDY SPONSOR AND FUNDER

The sponsor of the study is the University of Lincoln.

The Chief Investigator has overall responsibility for the study and shall oversee all study management.

## STUDY MANAGEMENT COMMITTEES

### Study Steering/Management Group

The Study Steering Committee shall meet every three months to ensure all practical details of the study are progressing and working well.

Academic team members conducting the study will meet monthly to discuss operational matters, either face-to-face or via teleconference.

# STUDY BACKGROUND and RATIONALE

Diabetes is increasing in prevalence, now affecting 5% of UK adults^3^. Efforts to improve diabetes control, using insulin and drugs to reduce complications, have led to increased rates of hypoglycaemia in people with diabetes^4^. Interruption of glucose supply to the brain causes cerebral dysfunction which, unless corrected promptly, can cause cognitive impairment, confusion, coma and, if prolonged, death.

Hypoglycaemia, a common adverse complication of diabetes treatment^5^, is often managed by patients themselves or their relatives, but severe hypoglycaemia (defined as cognitive impairment severe enough to require external assistance for recovery) frequently requires an ambulance resulting in Emergency Department attendance or hospital admission^6^. Severe hypoglycaemia constitutes around 1% of 1.7 million emergency ambulance calls in England and Scotland resulting in 100 thousand paramedic attendances and estimated costs in England of £13.6 million annually^7^.

Hypoglycaemia is associated with adverse consequences including higher mortality, morbidity and health service costs due to hospital attendance/admission^8 9 10^. It is also frightening for both patients and relatives and impairs quality of life and productivity, leading to poor long term control^11 12^.

A common accompaniment of insulin treated diabetes is impaired awareness (affecting around 25% of adults with type 1 and 10% of type 2 diabetes) when people experience reduced symptoms without having or recognising warning signs of impending hypoglycaemia. It increases the chance of a subsequent severe hypoglycaemic event by threefold^13^. Impaired awareness is more common in those who call an ambulance for hypoglycaemia with around half of type 1 diabetes individuals displaying features of reduced awareness^14^.

A systematic review highlighted that those with hypoglycaemia attended by ambulance services frequently have recurrent episodes, do not attend primary care when advised to do so by ambulance staff, but often require changes in therapy to prevent further episodes^15^. Recurrent hypoglycaemic episodes following ambulance calls are estimated to occur in 7.7% at 3 months and 17.7% at 6 months (data from Scottish Ambulance Service). The authors of the systematic review recommended development and evaluation of community referral pathways for hypoglycaemia^15^.

A systematic review and subsequent controlled before-and-after study in the Emergency Department concluded that information leaflets (booklets) can improve patients’ knowledge and satisfaction. For patients with acute conditions, leaflets can increase adherence to treatment^16 17^. Kumaran et al.^18^ also provide evidence to support the fact that patients with diabetes could be helped by providing them with well-designed educational leaflets which explain how to better manage their condition.

“Hypos can strike twice” is part of a complex quality improvement intervention involving ambulance staff providing treatment and advice to people who have had a hypoglycaemic attack to access follow-up care by the GP or specialist diabetes team, as detailed in national ambulance (JRCALC) clinical guidelines^1^, supported by the provision of a “Hypos can strike twice” booklet, which the patient can read when they are fully recovered from the cognitive and other effects of the hypoglycaemic episode.

**Description of the intervention**: The “Hypos can strike twice booklet” has a section where the paramedics record for the patient a summary of their physical condition both when the ambulance service arrives and when it departs. It also includes a section where the ambulance staff record details of the relevant treatment provided. We hope this will be useful to patients who may be confused during their hypos (and hence during the visit from the ambulance service) so that they can refer back to it later after their recovery. All patients receiving the booklet will be advised to seek further advice from their GP or local community diabetes services so that they have an opportunity to review with a health professional whether they require any changes in their usual diabetic medication/insulin. In addition to explaining to the patients what has happened to them, the booklet also provides advice about what to eat following a hypo and reminds them to avoid strenuous activities, alcohol and be cautious about driving during the first few hours of recovery. It also encourages them to undertake regular self-monitoring of their blood-glucose levels. FAQs are provided to explain in lay terms, what hypos are, the symptoms, causes, how to try to prevent them and what to do if they happen again. We hope that patients will find the booklet reassuring and serve as a useful and easy-to-read resource for them. It is hoped that this intervention will reduce the chances of the patients having further severe hypos and reduce ambulance attendances for this.

The ‘Hypo’s can strike twice’ intervention was delivered in successive county areas of East Midlands Ambulance Service NHS Trust (EMAS). Communications face-to-face, email and information publicised on an electronic bulletin (E-news), twitter and Facebook, advise staff to implement the booklet when visiting patients with diabetes who have experienced hypoglycaemia. Reminders are also provided to staff to complete the care bundle for hypoglycaemia and to refer patients to an appropriate healthcare professional following an episode of hypoglycaemia.

The intervention was rolled out by division (county) in EMAS in the following steps:

Step 1: October/November 2018, Leicester and Northamptonshire.

Step 2: January/February 2019, Nottinghamshire and Derbyshire.

Step 3: April/May 2019, Lincolnshire.

This study will evaluate the effect of implementing an ambulance clinician delivered hypoglycaemia intervention (‘Hypos can strike twice’) on repeat ambulance calls, attendances and transports to hospital and also explore how the intervention was delivered, the impact on staff and patients, the wider context in which it was delivered, and the opportunities and potential for scaling up this intervention more widely.

# STUDY OBJECTIVES AND PURPOSE

## PURPOSE

Aim: To evaluate the effect of implementing the ‘Hypo’s can strike twice’ intervention to patients with diabetes and hypoglycaemia attended by EMAS in the East Midlands region. “Hypos can strike twice” is a complex intervention involving ambulance staff providing treatment and advice to people who have had a hypoglycaemic attack to access follow-up care by the GP or specialist diabetes team as detailed in national ambulance (JRCALC) clinical guidelines^1^ supported by the provision of a “Hypos can strike twice” booklet which the patient can read when they are fully recovered from the cognitive and other effects of the hypoglycaemic episode.

## PRIMARY OBJECTIVE

To investigate the effect of implementing the ‘Hypo’s can strike twice’ on repeat ambulance calls and attendances for hypoglycaemia.

## SECONDARY OBJECTIVES

To investigate the effect of implementing the ‘Hypo’s can strike twice’ on:

1. Recorded referrals to an appropriate healthcare professional (e.g. GP, nurse).
2. Completed care bundle for hypoglycaemia (proportion of patients with all of blood glucose recorded before treatment, blood glucose recorded after treatment and treatment given for hypoglycaemia.
3. Costs of implementation ‘Hypo’s can strike twice’ intervention vs costs of health service resource use.
4. To conduct a process evaluation to explore how ‘Hypo’s can strike twice’ exerts its effects and can be scaled up if effective by understanding implementation, mechanisms of impact, and contextual factors using interviews and surveys.

# OUTCOME MEASURES/ENDPOINTS

## PRIMARY OUTCOME MEASURE/ENDPOINT

Repeat ambulance calls and attendances for hypoglycaemia within 14 days.

## SECONDARY ENDPOINTS/OUTCOMES

1. Repeat ambulance calls and attendance for hypoglycaemia within 30 and 90 days.
2. Recorded referral to an appropriate healthcare professional (e.g. GP, nurse).
3. Completed care bundle for hypoglycaemia (proportion of patients with all of blood glucose recorded before treatment, blood glucose recorded after treatment and treatment given for hypoglycaemia.
4. Costs of implementation of ‘Hypo’s can strike twice’.
5. Process evaluation to explore how ‘Hypo’s can strike twice’ exerts its effects and can be scaled up if effective by understanding implementation, mechanisms of impact, and contextual factors using interviews and surveys.

# Possible unintended outcomes

Possible unintended outcomes of the intervention may include poorer control of diabetes with a greater risk of microvascular complications but this has to be balanced with the risk of hypoglycaemia and patients’ preferences for treatment and quality of life.

# STUDY DESIGN

Non-randomised stepped wedge design with mixed methods process evaluation.

Work package (WP) 1 Stepped wedge: We will use routine anonymised data from routine call-and-dispatch and clinical records data from EMAS for 12 months before the intervention was first introduced (September 2017) to at least 6 months after the final step of the introduction in April 2019, i.e. October 2019. We will include call categories, timings, geographical location, together with demographic (age, sex) and clinical information, physiological measurements taken, treatments given, and whether the patient was referred to community services (general practitioner, community diabetes nurse or alternative) for their diabetes or transported to hospital by ambulance. Hypoglycaemia is recorded in electronic clinical records under ‘chief complaint’ or impression’ which will enable us to identify incidents of patients presenting with hypoglycaemia. Individual patients will be assigned a unique (non-personally identifiable) number in the anonymised dataset provided to the university which will enable us to identify repeat attendances for an individual patient.

WP2 Health economics: We will use a cost-consequences approach to estimate the costs of the intervention in relation to its effects. Total costs will be estimated, from an NHS perspective, using unit costs from NHS Reference Costs, Emergency Services Reference Costs, and other relevant costs, multiplied by resource units.

WP3 Survey: We will use a self-administered survey to understand implementation, mechanisms of impact, and contextual factors. We will use random sampling to select patients with hypoglycaemia who were attended stratified by geographical area, from the ambulance service user records and we will send them questionnaires by post (with a stamped addressed envelope for return to the University of Lincoln) or offer them the option to complete the questionnaire on-line, according to their preference. We will conduct an online survey to all front-line clinicians to assess attitudes, perceptions and behaviour towards the intervention including the booklet. We will also conduct a self-administered postal questionnaire to patients using a Patient Reported Experience Measure, previously developed and validated by [name] and colleagues^19 20^. The sample size calculation for the survey is included below.

WP4 Qualitative: We will conduct semi-structured interviews, as part of the process evaluation, to explore whether the introduction of the ‘Hypo’s can strike twice’ intervention was considered beneficial by participants, how acceptable the intervention was, and whether it was associated with any unanticipated issues. Through the use of interviews we will also assess the fidelity and quality of the implementation, as well as explore causal mechanisms and contextual factors. We will answer three main questions: What is implemented and how? How does the delivered intervention produce change? How does context affect implementation and outcomes?

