## DATA ANALYSIS

WP1 Stepped wedge: Dispatch data will be linked with clinical data using a unique job number. People included will be identified and tracked for repeat attendances. In the stepped wedge design, the intervention and control observation periods take the place of the treatment and control groups in a parallel trial and the distribution of results across unexposed observation periods is compared with that across the exposed observation periods. There are a small number of steps and so characteristics of the groups in the wedge can be compared by group, including number, the average cluster size, cluster characteristics, and important patient characteristics.

Following an intention-to-treat principle, clusters will be analysed according to their crossover time irrespective of whether crossover was achieved at the desired time. Under the stepped wedge design the evaluation happens over a period of time, during which the number of clusters exposed to the intervention gradually increases. This means that unexposed observations will, on average, be from an earlier calendar time than exposed observations. Additionally, policy and service delivery changes may occur. Calendar time is associated with both the exposure to the intervention and also possibly the outcome, and so is a potential confounder and will be adjusted for in the analysis.

A linear mixed model will be fitted adjusting for the systematically different observation periods and for clustering in the data. Time is included as a fixed effect and a random effect for cluster. The design also allows examination of the impact of the intervention changing over time once it is introduced into a cluster.

WP2 Health economics: We will use a cost consequences model, estimating costs from NHS Reference Costs to evaluate the costs of the intervention in relation to its effects. Key cost drivers associated with repeat hypoglycaemic episodes will be modelled.

WP3 Survey: We will analyse the overall experience of both patients and ambulance staff, as well as use descriptive statistics and comparisons between responder groups (e.g. ambulance staff vs patients; paramedics vs emergency medical technicians), where appropriate.

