### Inclusion Criteria

**Patients**

Young adults aged 16-17 years and adults aged 18 years+ with diabetes experiencing hypoglycaemia needing an ambulance service response. Hypoglycaemia for this study was identified as a ‘clinical impression’ of ‘hypoglycaemia’ or ‘diabetic problem’. Hypoglycaemia may also be identified according to ambulance guidelines^1^ as any blood glucose less than 4mmol/L.

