**RANDOMISATION AND BLINDING**

This study will not involve randomisation or blinding of participants or study personnel.

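### The effect model as written adjusts for calendar time and county group but not for the age, sex and call category already extracted, so county-specific or exposure-linked case-mix change stays in the estimate

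*Protocol*

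**What the plan says.** Protocol, DATA ANALYSIS (WP1), repeated in the STUDY SUMMARY, states the model: "A linear mixed model will be fitted adjusting for the systematically different observation periods and for clustering in the data". It then names the terms: "Time is included as a fixed effect and a random effect for cluster". Calendar time is the one confounder identified; the text says it "so is a potential confounder and will be adjusted for in the analysis". Patient characteristics appear in the same section in a different role: "characteristics of the groups in the wedge can be compared by group, including number, the average cluster size, cluster characteristics, and important patient characteristics".

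Protocol, STUDY DESIGN (WP1) lists the extraction, which includes call categories and "demographic (age, sex) and clinical information", together with physiological measurements and treatments.

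Protocol, RANDOMISATION AND BLINDING: "This study will not involve randomisation or blinding of participants or study personnel". Under Size of sample, the design is three county groups observed over 12 group-by-period cells, that is, four periods of about three months.

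Protocol, Inclusion Criteria (Patients): "Hypoglycaemia for this study was identified as a ‘clinical impression’ of ‘hypoglycaemia’ or ‘diabetic problem", with a blood glucose below 4 mmol/L as a further route.

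**The concern.** With three groups and a roll-out order that was not randomised, neither chance allocation nor the number of clusters protects against a change in who is in the data. Period effects and a cluster intercept deal with some kinds of case-mix difference but not with all.

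One route to an exposure-linked change is visible in the protocol. Cases are identified partly by the crew's recorded impression, and the background section says that staff communications and hypoglycaemia reminders come with the intervention. If the mix of attended or coded callers changes in a county around its crossover, the model as written attributes the resulting change in repeat calls to the intervention. Age, sex and call category, which could absorb part of this, are already in the dataset.

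**Working it through.** **Inputs from the protocol (Size of sample).** Three groups, four periods, ICC 0.1, pre-intervention repeat proportion 0.10, target 0.05. Calls per three months are attendances × 0.01 / 24:
- Leicestershire + Northamptonshire: 1,089,727 × 0.01 / 24 = 454
- Derbyshire + Nottinghamshire: 1,435,811 × 0.01 / 24 = 598
- Lincolnshire: 774,128 × 0.01 / 24 = 323

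These reproduce the stated counts.

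**Which shifts reach the estimate.** For cell means y(c,t) = period(t) + cluster(c) + θX(c,t) + error, generalised least squares gives θ̂ = Σ w(c,t) y(c,t). A case-mix change that adds δ(c,t) to the repeat proportion biases θ̂ by Σ w(c,t) δ(c,t). With the inputs above:
- In each period the weights sum to 0 over groups, so a shift common to all counties gives bias 0.
- Over periods the weights sum to 0.006, 0.000 and −0.006 for the three groups, so stable county differences nearly cancel.
- Over exposed cells the weights sum to 0.29, 0.47 and 0.24 for groups 1, 2 and 3 (total 1.00). A shift from crossover in one group passes through at that fraction. The same shift from crossover in every group passes through in full.
- If the cluster variance is estimated at zero, which can happen with three clusters, the group sums become 0.745, −0.104 and −0.641, and stable county differences no longer cancel.

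**Size of the bias (assumed inputs, not in the protocol).** Overall repeat risk 10%, 40% of callers at higher risk, risk ratio RR. Then p_low = 0.10 / (0.4 RR + 0.6), p_high = RR × p_low, and full-pass-through bias = shift × (p_high − p_low).

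| RR | p_low | p_high | Shift 5 points | Shift 10 points |
| --- | --- | --- | --- | --- |
| 1.5 | 8.33% | 12.50% | 0.21 | 0.42 |
| 2 | 7.14% | 14.29% | 0.36 | 0.71 |
| 3 | 5.56% | 16.67% | 0.56 | 1.11 |

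- Shift at exposure in every group: 0.21 to 1.11 points.
- Shift at crossover in one group only: from 0.21 × 0.24 = 0.05 to 1.11 × 0.47 = 0.52 points.
- Stable difference, with the share 10 points higher in group 1 and 10 lower in group 3, RR 2: at ICC 0.1, 0.71 × (0.006 + 0.006) ≈ 0.01 points; with cluster variance estimated at zero, 0.71 × (0.745 + 0.641) = 0.98 points.

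**Standard error of the effect.** With four periods it is 1.3 points if the total variance is 0.075 × 0.925 and the ICC takes 10% of it. It is 1.6 points if the residual variance is 0.10 × 0.90 with the cluster variance added on top. An assumed eight-period layout, using the full extraction window from September 2017 to October 2019, gives 1.2 to 1.4 points and single-group pass-through of 0.45, 0.35 and 0.19. The range is therefore about 1.2 to 1.6 points.

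**Comparison.** 1.11 points is about 0.7 to 0.9 standard errors and 1.11 / 5 = 22% of the target. 0.52 points is about 0.3 to 0.4 standard errors and 0.52 / 5 = 10% of the target.

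**The case against.** The protocol never says that nothing else enters the model, and a covariate list may sit in an analysis plan that is not shown. That is fair, and the absence of such a list would not by itself be a finding. What remains is that the protocol names the model's terms, names one confounder, and gives patient characteristics a descriptive role.

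A reader might infer that any case-mix difference between control and exposed periods biases the result. The model does not behave that way: common shifts cancel, and stable county differences nearly cancel at the stated ICC. A reader might also take 1.1 points as the likely bias. That figure needs the same 10-point shift at exposure in all three groups and a risk ratio of 3. The protocol gives no evidence for either, or for the 40% share.

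Two further objections stand. Adjustment addresses measured case mix only: impaired awareness, which the background links to a threefold risk of a further severe event, is not itemised in the extraction, nor is diabetes type. And a change in who is coded as hypoglycaemia is selection into the dataset, which covariates cannot fully repair. A gain in precision from adjustment is not shown and is not part of the case.

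**Conclusion.** The point holds in a limited form. The effect model as written leaves in the estimate any case-mix change that differs by county over time or begins with exposure. It leaves in stable county differences only if the cluster variance is estimated near zero. Under the assumed inputs the bias is about 0.05 to 0.5 points for a one-group shift and 0.2 to 1.1 points for a shift at exposure in every group. Either is small to moderate beside a standard error of 1.2 to 1.6 points, and neither could account for the 5-point target alone. The sample-size figures are not affected. The change is still worth making, because the design has no randomisation to rely on and the variables are already in hand.

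**What to change.** In DATA ANALYSIS (WP1) and the matching STUDY SUMMARY text, add age, sex and call category of the index call as fixed effects in the effect model, and report the time-and-cluster-only estimate beside it.

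Keep first blood glucose to a sensitivity analysis. Recording it before treatment is a component of the care bundle, and staff are reminded to complete that bundle as part of the intervention, so whether it is recorded can change with exposure. For the same reason, leave out referral, transport, treatment and advice.

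The cost is a change of analysis wording, with no new data. Records missing age, sex or call category will need a stated handling rule. The report should say that adjustment covers measured case mix only and does not correct a change in who is coded as hypoglycaemia.
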